#### Secondary outcome

The secondary outcome is the rational rate of antibiotic prescription defined as the reasonable amount of antibiotics prescribed during the study period divided by the total amount of antibiotics prescribed though the study period.

#### Sample size calculation

Since the outcome variable (antibiotic prescription rate per physician) is a continuous variable, we used the two independent means formula (two-tailed test) to calculate the required number of physicians to recruit into the study as given by the following formula.

$$n_{1}=\frac{{\left(z_{1-\frac{\alpha }{2}}+z_{1-\beta }\right)}^{2}\left[\sigma_{1}^{2}+\frac{\sigma_{2}^{2}}{r}\right]}{\Delta^{2}}$$

$$r=\frac{n_{2}}{n_{1}},\Delta =\mu_{1}-\mu_{2}$$

In the above formula, the parameters are as follows: α = 0.05, Z(0.975) = 1.96, β = 0.2, Z(0.8) = 0.84. Based on the data from our previous study, the pre-intervention mean (μ1) = 35.0, and the pre-intervention variance (σ1) = 15.0; the post-intervention mean (μ2) = 30.0, and the post-intervention variance (σ2) = 15.0 [39]. Since a 1:1 ratio was adopted in the experimental design, the sample size ratio (r) of the two groups was 1.0. From this we can calculate the sample size as n1 (group 1) = n2 (group 2) = 142 physicians per group.

To allow for a 10% non-response rate, the sample size was increased to 160 physicians per group for a total of 320 physicians. Since most of these primary hospitals have 3–4 outpatient physicians who meet the inclusion criteria, we will randomly select hospitals using a computer-generated number from the list of 132 hospitals that met the inclusion criteria. The total number of hospitals to be included in the study will be determined by whether the hospitals have 320 outpatient physicians who meet the inclusion criteria. We will visit the selected hospitals and ask the physicians to sign the informed consent form. Fig 4 shows a flow chart of the trial where group 1 represents the group of physicians who will receive the intervention in the first stage.

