**Methods:**

We will pilot and develop a cluster-randomised, open controlled, crossover, superiority trial. A total of 320 outpatient physicians in 6 counties of Guizhou province who met the standard will be randomly divided into intervention group and control group with a primary care hospital being the unit of cluster allocation. In the intervention group, the three components of the feedback intervention included: 1. Artificial intelligence (AI)-based real-time warnings of improper antibiotic use; 2. Pop-up windows of antibiotic prescription rate ranking; 3. Distribution of educational manuals. In the control group, no form of intervention will be provided. The trial will last for 6 months and will be divided into two phases of three months each. The two groups will crossover after 3 months. The primary outcome is the 10-day antibiotic prescription rate of physicians. The secondary outcome is the rational use of antibiotic prescriptions. The acceptability and feasibility of this feedback intervention study will be evaluated using both qualitative and quantitative assessment methods.

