### Process

A complete trial process is shown in Fig 1. To avoid selection bias [47] we will use a crossover design in which each group will receive different treatments at different times [48]. We will divide outpatient physicians in each selected primary care institution equally into two sequences according to the principle of randomization.

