### Randomization and blinding

After recruitment, the information technology staff of LWTC will be invited to randomly assign (computer-generated random numbers) all recruited primary care institutions to an intervention group and a control group in a ratio of 1:1.

Since this is a behavioural intervention trial, the physicians will have a clear idea of the intervention when they sign the informed consent form and will be able to determine whether they are in the intervention or control group at the start of the trial. Therefore, the design of this study makes it impossible to use a blinded approach to participants and researchers [39].

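### The 142 physicians per group come from a formula for independent physicians in two parallel groups, so the stated 80% power is not the power of this hospital-randomised crossover design

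*Protocol article*

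**What the plan says.** **Unit of allocation.** The abstract describes randomisation "with a primary care hospital being the unit of cluster allocation". Randomization and blinding agrees: a computer-generated list assigns "all recruited primary care institutions to an intervention group and a control group in a ratio of 1:1". The Process section says something different: "We will divide outpatient physicians in each selected primary care institution equally into two sequences according to the principle of randomization".

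**Sample size.** Under Sample size calculation, "we used the two independent means formula (two-tailed test) to calculate the required number of physicians to recruit into the study". The inputs are "α = 0.05, Z(0.975) = 1.96, β = 0.2, Z(0.8) = 0.84", then "the pre-intervention mean (μ1) = 35.0, and the pre-intervention variance (σ1) = 15.0" and "the post-intervention mean (μ2) = 30.0, and the post-intervention variance (σ2) = 15.0", with equal groups. The result is 142 per group, raised to 160 (320 in total) for 10% non-response. The number of hospitals is whatever supplies 320 physicians, given that "most of these primary hospitals have 3–4 outpatient physicians who meet the inclusion criteria".

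**Analysis.** Statistical analyses plans t, paired t, signed-rank or rank-sum tests between groups at baseline, at the crossover point and at the end, and within groups over time. It adds a transition model for change within the same physician. None of these is said to account for hospital. The limitations paragraph of the Discussion acknowledges carry-over and residual seasonality, and says a washout cannot remove the former.

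**The concern.** The article prints the calculation in full: formula, inputs, result and inflation. The mismatch is therefore in the text and is not a detail left to an analysis plan. The formula is for two parallel groups of independent units. The stated design differs in two ways that pull in opposite directions:

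- Allocating hospitals makes colleagues' outcomes correlated, which raises the variance of a between-group comparison.
- Crossing hospitals over allows a within-hospital comparison, which lowers it.

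Neither enters the calculation, so 80% describes neither comparison.

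Two things are at stake. If the between-group comparison is properly adjusted for hospital, a null result may be read with more confidence than the trial supports. If it is tested as though physicians were independent, a false positive becomes more likely than the nominal 5%.

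**Working it through.** **1. Reproduce the plan's figure.** With Δ = 35.0 − 30.0 = 5 and σ = 15 in both groups:

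n = (1.96 + 0.84)² × (15² + 15²) / 5² = 7.84 × 450 / 25 = 141.1, so 142.

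This matches exactly. The 15.0 is labelled a variance but enters as a standard deviation; a variance of 15 would give 10 per group. Power at 142 is 80.2%, so there is no hidden allowance for clustering.

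**2. Between-group comparison at the crossover point, adjusted for hospital.** The design effect is DE = 1 + (m − 1) × ICC, and power = Φ(5 / (15√(2·DE/142)) − 1.96). Cluster size m = 3–4 is from the sample size section; 3.5 is the midpoint. The article gives no ICC, so the values below are assumptions. The minimum detectable difference (MDD) at 80% power is 2.80 × 15 × √(2·DE/142).

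| Assumed ICC (m = 3.5) | DE | Power at 142 | Power if all 160 are kept | n per group, 142 × DE | MDD at 142 |
|---|---|---|---|---|---|
| 0.05 | 1.125 | 75% | 80% | 160 | 5.3 |
| 0.10 | 1.25 | 71% | 76% | 178 | 5.6 |
| 0.20 | 1.50 | 63% | 68% | 213 | 6.1 |

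For example, at ICC 0.10: 15√(2.5/142) = 1.990; 5/1.990 = 2.512; Φ(2.512 − 1.96) = Φ(0.552) = 0.71. The needed n is before any inflation for non-response. Across m = 3–4 and ICC 0.05–0.30, DE runs from 1.10 to 1.90 and power at 142 from 76% to 53%.

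**3. Two-period analysis, same physicians in both periods.** Relative to the independent parallel comparison, the variance is multiplied by [1 + (m − 1)ρ − r − (m − 1)η] / 2. Here ρ is the within-period ICC, r the correlation of a physician with himself or herself across periods, and η the cross-period correlation between colleagues. With m = 3.5 and r = η = 0:

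| Assumed ρ | Variance factor | Power at 142 |
|---|---|---|
| 0.10 | 1.25/2 = 0.625 | 94% |
| 0.20 | 1.50/2 = 0.750 | 90% |
| 0.30 | 1.75/2 = 0.875 | 85% |

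In the cases computed with positive between-period correlations, power is higher still. All of this presumes no carry-over.

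**4. Between-group tests with no adjustment for hospital.** If the standard error omits DE, the actual two-sided type I error is 2[1 − Φ(1.96/√DE)]:

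- DE 1.10: 1.96/1.049 = 1.869, giving about 6%.
- DE 1.25: 1.96/1.118 = 1.753, giving about 8%.
- DE 1.90: 1.96/1.378 = 1.422, giving about 16%.

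Power of the unadjusted test changes much less: about 79%, 78% and 73% for the same three values.

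**The case against.** A reader might infer that the trial is underpowered. The document does not support that without qualification. The crossover is the declared design, the plan includes paired comparisons and a within-physician model, and step 3 shows that a valid two-period analysis could exceed 80% at 142 per group even with no between-period correlation. Adjusting for each physician's own baseline rate could also recover power. With an assumed baseline correlation of 0.6, taken as equal at physician and hospital level, power at DE 1.25 returns to about 88%, although at DE 1.90 it reaches only 72%. This part of the objection stands and limits the claim about direction. It does not rescue the printed 80%: the calculation contains no crossover or baseline term, and the Discussion concedes carry-over without a washout.

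Nor can the formula be tied firmly to the crossover-point comparison. Its inputs are labelled pre- and post-intervention, and the section names no contrast. That comparison is simply the planned one that most resembles two parallel groups.

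The Process section splits physicians within each institution. If that were the real allocation, the between-hospital penalty in step 2 would not apply. The title, the abstract and the randomisation section all point to hospital allocation, so the concern stands on that reading and is conditional on it.

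Finally, clusters are small and the penalty may be modest: at ICC 0.05 and m = 3.5, keeping all 160 per group gives 80%. The graph neural network section also mentions a multi-level model in passing, and an unseen analysis plan might specify hospital effects. The type I error figures therefore apply only if the tests are run as the article describes them, without such adjustment.

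**Conclusion.** The concern holds in a limited form. The arithmetic is correct, but the formula does not match the stated design, so 80% power at 142 per group is unsupported.

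- For a hospital-adjusted comparison at the crossover point, power is about 75%, 71% or 63% at ICC 0.05, 0.10 or 0.20.
- For a two-period analysis free of carry-over, it is about 94% to 85% at within-period ICC 0.10 to 0.30, with between-period correlation set at zero.
- For between-group tests unadjusted for hospital, type I error is about 6% to 16% at design effects 1.10 to 1.90.

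The ICCs and correlations are assumptions; only the cluster size of 3–4 comes from the article. All three results rest on hospitals being the unit of allocation.

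**What to change.** 1. Reconcile the Process section with the abstract and the randomisation section on whether hospitals, or physicians within hospitals, are allocated.
2. If hospitals are allocated, keep the 320 physicians and restate the power or minimum detectable difference with a stated ICC and between-period correlation. Both should be estimable from the previous trial's health information system data, since that trial already supplies the means and spread. Give the result separately for the first-period contrast and for the crossover contrast.
3. Make the analysis match: a baseline-adjusted model that accounts for hospital, by a random effect or cluster-robust standard errors. Restating the power while keeping unadjusted tests would only create a new inconsistency.
4. In the same paragraph, call σ = 15.0 a standard deviation.

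The cost is a recalculation from data the team should already hold, plus revised sample size and analysis paragraphs. No extra physicians are asked for. The downside is that the stated power may be less favourable than 80%.

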**Fig 4 pone.0259065.g004:**
[figure not shown]
Flow chart of the crossover trial.

### Statistical analyses

We will follow the statistical method of the previous study [39]. Descriptive statistics will be presented for the outcome variables and related covariates. We will compare the antibiotic prescription rate and the antibiotic prescription rationality rate between the two groups (Group 1 and Group 2) at baseline, crossover point and at the end of the trial. After testing of the data for normality, Student’s t-test, paired t-test, Wilcoxon signed-rank test or Rank-sum test will be used to compare antibiotic prescription rate and antibiotic rationality rate between the two groups for horizontal (between groups) comparison or vertical (at different time points within the same group) comparison, to observe the difference and trend of change. Secondly, because it will take some time before feedback interventions have any impact on antibiotic prescription rates, a transition model suitable for studies that includes regular follow-up intervals and changing exposure and outcome states will be used to predict the impact of the intervention on changes in antibiotic prescription rates and rationalization rates within the same physician over time. The transition model ensures that the "carry-over" impact is adjusted and that correlations over time are addressed.

Following ITT principles [49], outpatient physicians from all participating primary care facilities will be included in the analysis. We will report all results according to the CONSORT guidelines [50].

All data analyses will be done using R version 4.0.4

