### Outcome measures

#### Primary outcome

The primary outcome is the 10-day antibiotic prescription rate of physicians defined as the number of antibiotic prescriptions divided by the total number of prescriptions in each 10-day time period (the term “prescription” as used here refers to one drug) [39]. Indicators of related covariates include: 1. Baseline characteristics of the physician, such as age, gender, job title, education, and working years; 2. Patient characteristics, such as gender, age, ethnicity, and disease; 3. Antibiotic information, such as name, dosage form, route, and amount in grams.

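### If hospitals are the allocated unit, the named t-tests and rank tests on physician rates ignore clustering, and the between-group comparisons exceed their nominal 5% error

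*Protocol article*

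**What the plan says.** **Allocation.** The title calls the trial cluster-randomised. The Abstract describes randomisation "with a primary care hospital being the unit of cluster allocation", and the Randomization and blinding section assigns "all recruited primary care institutions to an intervention group and a control group in a ratio of 1:1". The Process section says something different: "We will divide outpatient physicians in each selected primary care institution equally into two sequences according to the principle of randomization".

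**Outcome.** "The primary outcome is the 10-day antibiotic prescription rate of physicians". The secondary outcome, the rational rate of antibiotic prescription, is compared between the same groups.

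**Analysis.** The Statistical analyses section compares the groups at baseline, at the crossover point and at the end. After a normality check it names the two-sample t-test and adds: "paired t-test, Wilcoxon signed-rank test or Rank-sum test will be used to compare antibiotic prescription rate and antibiotic rationality rate between the two groups". The comparisons run either across groups or over time within a group. It then adds a transition model to predict the intervention's impact on "changes in antibiotic prescription rates and rationalization rates within the same physician over time", stated to adjust for carry-over and to ensure that "correlations over time are addressed".

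**Clustering.** The Statistical analyses section mentions no hospital effect, hospital-level summary or cluster-robust variance. A multi-level model is mentioned once, in the section on graph neural network technology, without levels, and is not taken up in the analysis section. That section also refers to the method of the previous trial, which is not at hand.

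**The concern.** When whole hospitals are allocated, physicians of one hospital always fall in the same arm. If their prescribing rates are positively correlated, 160 physicians per group carry less information than 160 independent physicians. An ordinary t-test or rank-sum test on physician rates does not see this. It uses too small a standard error and rejects a true null hypothesis more often than 5% of the time.

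Some correlation is plausible from the article itself: the ranking pop-up compares each physician with colleagues of the same outpatient department, and these colleagues serve the same township population. The transition model, as described, deals with repeated measurements of one physician, which is a different correlation.

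At stake is the two-sided 5% error rate assumed in the sample size section, for both outcomes, wherever a between-group test of this kind is used to draw a conclusion.

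**Working it through.** **Inputs from the Sample size calculation section:** two-sided α = 0.05 (z = 1.96), 80% power (z = 0.84), means 35.0 and 30.0, spread 15.0 in both groups (labelled a variance, but it works in the formula as a standard deviation), 10% non-response, and mostly m = 3–4 eligible physicians per hospital. **Assumed:** ICC 0.01–0.20, because the article gives none.

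**1. The plan's own figure.** n = (1.96 + 0.84)² × (15² + 15²) / 5² = 7.84 × 450 / 25 = 141.1, so 142 per group, as stated. 142 / 0.9 = 157.8, so 158; the plan takes 160. No design effect enters, so the sample size also treats physicians as independent.

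**2. Between-group test under hospital allocation.** Design effect DE = 1 + (m − 1) × ICC. True type I error of the nominal 5% test = 2 × [1 − Φ(1.96 / √DE)]. An interval that ignores hospital is too narrow by 1 − 1/√DE. Example, ICC 0.10 and m = 4: DE = 1.30, √DE = 1.140, 1.96 / 1.140 = 1.719, type I error 8.6%.

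| ICC (assumed) | m | DE | √DE | Type I error | Interval too narrow by |
|---|---|---|---|---|---|
| 0.01 | 3 | 1.02 | 1.010 | 5.2% | 1% |
| 0.01 | 4 | 1.03 | 1.015 | 5.3% | 1% |
| 0.05 | 3 | 1.10 | 1.049 | 6.2% | 5% |
| 0.05 | 4 | 1.15 | 1.072 | 6.8% | 7% |
| 0.10 | 3 | 1.20 | 1.095 | 7.4% | 9% |
| 0.10 | 4 | 1.30 | 1.140 | 8.6% | 12% |
| 0.20 | 3 | 1.40 | 1.183 | 9.8% | 15% |
| 0.20 | 4 | 1.60 | 1.265 | 12.1% | 21% |

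Simulation under the null (4,000 trials per setting, 160 physicians per group, whole hospitals of 4) agrees. For ICC 0.05, 0.10 and 0.20 the t-test rejected in 6.5%, 8.0% and 12.3% of trials, and the rank-sum test in 6.4%, 8.3% and 11.9%.

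**3. Paired tests.** A constant hospital effect cancels in a within-physician difference, so the ICC of the rates does not carry over. What counts is the ICC of the changes. If that ICC were 0.05, 0.10 or 0.20, the simulated error of the paired t-test is 6.8%, 8.1% or 13.2% (m = 4); if it were zero, there is no inflation from this source.

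**4. The Process section read literally.** If the physicians of each hospital are split between the sequences, hospital effects balance across arms and the unadjusted test errs the other way. With m = 4, the simulated t-test error is 4.0% at ICC 0.10 and 3.2% at ICC 0.20.

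**5. Power of a parallel comparison at one time point, 142 per group.** With independent physicians it is 80.2%. For m = 3 and m = 4 it is 76.4% and 74.5% at ICC 0.05, 72.7% and 69.3% at 0.10, and 66.1% and 60.3% at 0.20. Keeping 80% would take 145 (DE 1.02) to 227 (DE 1.60) per group before non-response.

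**6. Why hospital and physician random effects alone are not enough.** Constant hospital and physician effects cancel from a two-period crossover contrast, so these terms do not protect it against variation that is specific to a hospital in one period. With 4 physicians × 9 ten-day windows = 36 observations per hospital and period, hospital-by-period variance equal to a share v of the residual variance inflates the true variance by 1 + 36v. For assumed v of 1%, 2% and 5% this is 1.36, 1.72 and 2.80, which gives type I errors of about 9%, 14% and 24%. A simulation with 80 hospitals gave 8.9%, 13.6% and 24%.

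**The case against.** **The allocation text is not uniform.** The Process section can be read as a within-hospital split, and then the direction reverses (step 4). This stands as a condition on the point. The title, the Abstract and the Randomization and blinding section favour hospital allocation, but the conflict has to be resolved in the text.

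**Clustering may be handled elsewhere.** The multi-level model and the reference to the previous trial's method leave that possible. Neither cures the problem: the first is a passing phrase with no levels, and the second cannot be checked here and does not change the tests that the article names. Because the tests are named for both outcomes, this is also not detail left to an unseen analysis plan.

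**The tests may not be decisive.** A reader might infer that the trial could declare superiority from hospital-to-hospital variation alone. The article does not support that. It presents these tests as showing differences and trends, uses the transition model to predict impact, and designates no test as deciding superiority. Nor can the transition model's error be quantified from its description.

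**Crossover designs cancel hospital effects.** This is true of paired within-physician differences. It is not true of the between-group comparison at the crossover point, which is a parallel comparison.

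**The size is unknown.** This also stands. With so few physicians per hospital the inflation is modest for a small ICC and negligible at 0.01.

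**Conclusion.** The point holds on condition that hospitals are the allocated unit. The between-group tests named for both outcomes are then anti-conservative for any positive within-hospital correlation. The direction is firm. The size rests on an assumed ICC: 6.2%–6.8% at 0.05, 7.4%–8.6% at 0.10 and 9.8%–12.1% at 0.20, for 3–4 physicians per hospital. The statement on intervals applies to any interval derived from these tests; the article itself names none.

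Two stronger readings are not supported. These percentages do not apply to the paired tests unless the changes themselves have such an ICC. And nothing in the article establishes a large ICC: shared drug stock or local norms, for example, are not described in it.

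Under either reading of the allocation, a between-group test that ignores hospital does not hold its nominal 5% when the ICC is positive, so the analysis should account for hospital in any case.

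**What to change.** 1. Reconcile the Process section with the Abstract and the Randomization and blinding section, and state one unit of allocation.
2. For both outcomes, base inference on one of the following:
   - a model of the physician rates with an intervention term and time effects (10-day window or period), fitted by GEE with hospital-clustered robust standard errors;
   - a mixed model with the same fixed terms and random effects for hospital, hospital-by-period and physician;
   - an analysis of hospital-by-period summaries.
3. Keep the t-tests and rank tests as descriptive only.
4. Restate the power for a stated, assumed ICC, since 80% with 142 per group presumes independent physicians.

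The number of hospitals should be adequate for robust errors: about 320/4 = 80 to 320/3 = 107. The cost is mainly analysis wording. P-values and intervals may become somewhat less favourable, and the restated power may fall below 80% for a parallel comparison.

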Despite these advances, our study will inevitably follow the limitations of previous studies. Firstly, infectious diseases in the southwest of China show a seasonal pattern. Our intervention trial will begin in April 2021 and continue for six months. Therefore, seasonal effects may not be completely eliminated during the trial period. Secondly, in the field of epidemiological trials and infection prevention, changes in subjects’ behavior due to the Hawthorne effect will have a certain impact on the results. Finally, when the trial moves from the first stage to the second stage, the experimental conditions of the subjects are changed, which may affect the results due to the carry-over effect. Since the feedback intervention trial in this study is a behavioral intervention trial, it is difficult to eliminate the behavior once it is developed, so the effect cannot be eliminated by setting a washout period as commonly implemented in drug intervention trials.

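### Within-group tests over time stand unranked beside the randomised comparison, with no calendar-period term stated, so a seasonal shift could produce a significant result without any intervention effect

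*Protocol article*

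**What the plan says.** All references are to the protocol article.

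- **Statistical analyses.** Groups 1 and 2 are to be compared at baseline, at the crossover point and at the end of the trial, on both the antibiotic prescription rate and the rationality rate. Depending on a normality check, t-tests or rank tests, paired or unpaired, are used either between groups or for a "vertical (at different time points within the same group) comparison, to observe the difference and trend of change". The section does not say which of the two carries the conclusion. It adds a transition model for change within the same physician over time, said to deal with carry-over and serial correlation. No term for season or calendar period is stated.
- **Discussion, limitations.** Infectious diseases in the region are described as seasonal, and "seasonal effects may not be completely eliminated during the trial period". A washout is ruled out because learned behaviour persists.
- **Data collection and management; Process.** Data run from April to October 2021, in two stages of three months with a crossover between them.
- **Sample size calculation.** The design difference is written as a before-after change: "the pre-intervention mean (μ1) = 35.0, and the pre-intervention variance (σ1) = 15.0", then "the post-intervention mean (μ2) = 30.0, and the post-intervention variance (σ2) = 15.0".

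**The concern.** A paired test of one group at two dates estimates the intervention effect plus everything else that changed between those dates. Over April to October that includes season, which the protocol itself expects to matter. It also includes any secular trend and any response to being observed. Randomisation gives no protection, because the control group does not enter the calculation.

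The between-group comparison at one date does not have this problem, since a shift shared by both groups subtracts out. The protocol plans both kinds of test for the same outcomes and gives neither priority. If the two disagree, nothing in the text says which prevails.

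The same question arises for the transition model. It is directed at change within a physician over time, and serial correlation and carry-over are the only features it is said to handle. Neither is an adjustment for calendar time.

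At stake is a report in which a within-group fall carries a small p-value while the randomised difference is close to nil. If prescribing rises with season, the reverse could happen and a real effect would be hidden.

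**Working it through.** **1. The plan's own figure.** Inputs from Sample size calculation: "α = 0.05, Z(0.975) = 1.96, β = 0.2, Z(0.8) = 0.84"; means 35.0 and 30.0, so Δ = 5; spread 15.0 in both groups; "the sample size ratio (r) of the two groups was 1.0".

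n per group = (1.96 + 0.84)² × (15² + 15²) / 5² = 7.84 × 450 / 25 = 141.12, rounded up to 142. This agrees with the protocol. It works only with 15.0 as a standard deviation, although the text calls it a variance; I therefore use SD 15 below. For 10% non-response, 142 / 0.9 = 157.8, or 158 against the stated 160 per group. I use 160.

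**2. What each comparison estimates.** Let τ be the intervention effect in stage 1 and s a seasonal change from baseline to the crossover point that is the same in both groups.

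- Group 1, within-group change: s + τ
- Group 2, within-group change (control in stage 1): s
- Group 1 minus Group 2 at the crossover point: τ

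With τ = 0, the within-group test in either group is a test of s alone.

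**3. How often the within-group test rejects when τ = 0.** For within-physician correlation ρ (assumed):

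SE of the mean change = 15 × √(2(1 − ρ)) / √160

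P(reject) = Φ(s/SE − 1.96) + Φ(−s/SE − 1.96)

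For s = 3 and ρ = 0.3: SE = 17.75 / 12.65 = 1.403; 3 / 1.403 = 2.138; Φ(0.178) = 0.571. For s = 3 and ρ = 0.8: SE = 9.49 / 12.65 = 0.750; 3 / 0.750 = 4.0; Φ(2.04) = 0.979. The second term is negligible in both.

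| ρ (assumed) | SE | s = 1 | s = 2 | s = 3 | s = 5 |
|---|---|---|---|---|---|
| 0.3 | 1.403 | 11% | 30% | 57% | 95% |
| 0.5 | 1.186 | 13% | 39% | 72% | 99% |
| 0.7 | 0.919 | 19% | 59% | 90% | 100% |
| 0.8 | 0.750 | 27% | 76% | 98% | 100% |

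The columns are assumed seasonal falls in percentage points. The last equals the design difference. A rise of the same size gives the same rejection rate with the opposite sign.

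**4. The concurrent comparison under the same conditions.** In a simulation of 4,000 trials per setting (160 per group, ρ = 0.5, normal data, no hospital clustering, τ = 0), the between-group t-test rejected in 4.5% to 5.3% of trials for falls of 0, 1, 2, 3 and 5 points. This held for follow-up values and for changes from baseline. The within-group paired test rejected in 5%, 13%, 39%, 72% and 99%, in line with the formula.

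**5. What clustering would change.** These calculations treat physicians as independent. Hospitals are randomised, so correlation within hospitals would lower the within-group figures somewhat when s > 0 and would push an unadjusted between-group t-test above 5%. The cancellation of s between groups does not depend on this, but the test of τ must allow for it.

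**The case against.** The strongest reply is that the protocol does not claim what a critic might read into it.

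- **Purpose of the tests.** A reader might infer that the within-group tests are meant as evidence of effect. The text does not say so; it gives their purpose as observing differences and trends. This stands, and the point must not be put more strongly than that the tests are unranked.
- **The control is kept.** A concurrent comparison is planned at three dates and is listed before the within-group one. A fall common to both groups would also show in Group 2 during stage 1, while it is the control. After crossover, a seasonal fall in Group 1 would mask loss of effect and would not imitate benefit. This stands for stage 1. In stage 2, Group 2's fall would coincide with its own intervention, and a continuing fall in Group 1 could be read as the persistence of behaviour that the Discussion expects.
- **The previous trial.** A reader might take the fall in both groups over six months, reported in the Background, as a sign of seasonal confounding. It is not: by then both groups of a crossover trial had received the intervention, so a true effect would look the same.
- **Multiplicity.** One might count every possible test and multiply up a familywise error rate. The article does not fix the number of within-group tests, the tests share physicians and dates, and a baseline comparison cannot yield a false claim of effect. No such figure is supported.
- **An unseen analysis plan.** Model covariates are commonly left to it, and a period term may be there. This is fair. What remains is a choice that the article does state: inferential within-group tests, on the same footing as the randomised comparison.

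**Conclusion.** The point holds in limited form. The article plans within-group significance tests over a period in which it expects seasonal change, does not place them below the randomised comparison, and states no calendar-period term for the transition model. Their p-values cannot separate season from intervention.

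Under no intervention effect and an assumed common fall of 3 points, such a test would be significant in about 57% to 98% of trials for ρ from 0.3 to 0.8, against about 5% for the concurrent contrast. For an assumed fall of 2 points the range is 30% to 76%.

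The documents give neither the size nor the direction of any seasonal shift, nor the within-physician correlation. The calculation also assumes that the shift is the same in both groups and ignores hospital clustering. It therefore shows how far a within-group test can mislead, not that this trial's result will be wrong.

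**What to change.** Change the Statistical analyses text as follows.

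1. Report within-group changes as estimates with intervals and plots by 10-day window, without p-values.
2. Drop the significance test at baseline and describe the groups instead.
3. Base the effect claim on the randomised between-group comparison, from a model with a fixed effect for each 10-day calendar window and allowance for clustering by hospital. At a single date the comparison is already concurrent; the window terms keep it so when data from many windows and both stages are pooled. If the transition model is kept, give it the same calendar terms.
4. Report the stage-1 contrast, at the crossover point, as the one free of carry-over. Resting the whole claim on it would set aside stage 2; that is a trade-off for the investigators to decide, and this point does not require it.

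The cost is small: a revision of the analysis wording, fewer p-values and a few more model terms. No additional data are needed. The model removes only the part of season, or of any response to observation, that both groups share.
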